**Design:**

All Italian doctors naïve to ECCE will be randomised to three groups. Group one will have access to ECCE for *Clinical Evidence *chapters and vignettes lot A and will provide control data for *Clinical Evidence *chapters and vignettes lot B; group two vice versa; group three will receive the concise printed version of *Clinical Evidence*. There are in fact two designs: a before and after pragmatic trial utilising a two by two incomplete block design (group one versus group two) and a classical design (group one and two versus group three). The primary outcome will be the retention of *Clinical Evidence *contents assessed from the scores for clinical vignettes selected from ECCE at least six months after the intervention. To avoid test-retest effects, we will randomly select vignettes out of lot A and lot B, avoiding repetitions. In order to preserve the comparability of lots, we will select vignettes with similar, optimal psychometric characteristics.

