### Study design

This is a before and after pragmatic randomised controlled trial utilising a two-by-two incomplete block design. When evaluating educational interventions aimed at improving clinical practice, a number of non-specific effects may influence estimates of the effect of an intervention, grouped together under the term Hawthorne effect [13-17]. These include positive attention effects, caused by participants knowing that they are the subject of a study, but also negative and demotivating effects, caused by being allocated to a control rather than an intervention group. If these non-specific effects are imbalanced across study groups in a quality improvement trial, the estimates may be biased. Randomised controlled trials using balanced incomplete block designs should balance such non-specific effects [13,15,17-20].

Because the Hawthorne effect may influence the outcome, this trial will adopt a two-by-two balanced incomplete block design in which subjects will be randomised into two groups. Group one will have access to ECCE for *Clinical Evidence *chapters and vignettes lot A and will provide control data for *Clinical Evidence *chapters and vignettes lot B. Group two will have access to ECCE for lot B and will provide control data for lot A. The design will be balanced because it ensures that all participants receive the same intensity of educational intervention and data collection, which should therefore balance any non-specific effects. The design will be incomplete because not all participants receive the complete education for all chapters and vignettes [14,17]. To check for a possible Hawthorne effect we will add a third control arm (classical design), with only a minimal intervention consisting of one of the elements of the complete intervention, namely the concise printed version of *Clinical Evidence *and access to the on-line full-text version. This group will not have access to the ECCE platform nor the clinical vignettes related to *Clinical Evidence*. The incomplete block design will answer the question "Does ECCE increase physicians' basic knowledge about EB information," while the classical design will answer the question "Is ECCE superior to the printed version of *Clinical Evidence." *Table 1 summarises the block and the classical designs.

**Table 1 T1:** Designs, hypotheses per trial, and possibility of ensuring equal Hawthorne effect across the arms.

Trial comparison	Design	Hypothesis	Hawthorne

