Arm I vs. II Complete intervention on lot A. Using lot B as control.	Block	If the test scores related to lot A vignettes increase in accordance with *Clinical Evidence *chapters A and there is no change in test scores of B chapters, the intervention has a genuine effect.	No
Arm II vs. I Complete intervention on lot B. Using lot A as control.	Block	If the test scores related to lot B vignettes increase in accordance with *Clinical Evidence *chapters B and there is no change in test scores of A chapters, the intervention has a genuine effect.	No
Arm I vs. III Complete intervention for lot A (ECCE). Minimal intervention on A-B chapters (*Clinical Evidence*) (control).	Classical	If the test scores related to A vignettes in the intervention arm increase in accordance with the *Clinical Evidence *chapters A and there is no change in the control arm the intervention (ECCE) has a favourable effect, but without controlling for the Hawthorne effect.	Yes
Arm II vs. III Complete intervention for lot B (ECCE). Minimal intervention on A-B chapters (*Clinical Evidence*) (control).	Classical	If the test scores related to lot B vignettes in the intervention arm increase in accordance with the *Clinical Evidence *chapters B and there is no change in the control arm the intervention (ECCE) has a favourable effect, but without controlling for the Hawthorne effect.	Yes

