### Outcomes measures and measurements

The primary outcome will be basic knowledge of the *Clinical Evidence *contents assessed through the scores from the clinical vignettes. The test will consist of fixed and multiple-choice questions from the selected valid, reliable vignettes and will be administered before (pre-test), immediately after (approximately 16 weeks after enrolment, post-test one), and six months after the intervention (approximately 36 weeks after enrolment, post-test two) (see Figure 6).

To reduce the risk of a test-training effect (practice effects or memory of the first administration will influence post-test performance) at each test section ('pre-test', 'post-test one' and 'post-test two'), we will randomly select two vignettes from lot A and two from lot B to avoid repetition. Therefor, each participant will have only a limited probability (approximately zero) of test/re-testing the same vignette from one assessment to another. The questionnaire will investigate the same *Clinical Evidence *knowledge for intervention and control chapters. This random sampling of outcomes with high psychometric standards will eliminate any interactions between the causal relationship and the classes of outcomes studied or not studied within the same group of vignettes [25]. To prevent participants from guessing which vignettes will be evaluated, we will add a number of "distracter" vignettes to lots A and B. All groups will also rate their satisfaction with the information source and its perceived value for their medical education and clinical practice.

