### Statistical analyses

Knowledge test data will be analysed using repeated-measure analyses of variance (ANOVA), reporting the partial omega squared (ù2) effect size with corresponding 95% confidence interval. Scores for the    knowledge test scale will be subjected totwo-by-three [TO TWO-BY-THREE] repeated-measures ANOVA having: 1) one between-subjects factor (ECCE lot A and ECCE lot B) and one within-subject factor (pre-test, post-test one and post-test two) for the incomplete block design trial; 2) one between-subjects factor (ECCE set and control) and one within-subject factor (pre-test, post-test one and post-test two) for the classical trial. Tests of Sidak-adjusted simple main effects will be used for post-hoc mean comparisons as needed. Orthogonal planned contrasts will be formulated for the knowledge test data to verify knowledge retention. We do not expect the data sets to follow normal distributions and assumptions completely. If this is the case, we will do nonparametric and robust analyses to explore differences in medians or distributional shapes. If nonparametric analysis yields similar interpretations and conclusions, we will focus on the parametric results.

Additional analyses will include examination of the relationship between knowledge test outcomes and potential moderator variables including sex, age, and years of practice, speciality (*e.g*., general internal medicine versus general surgery); preferred CME format; computer skills; ease using the internet; familiarity with and readiness to use EB information; study drop-out; satisfaction with learning experience, and frequency of attending residential and distant CME activities. For these analyses, we will use parametric methods (regression, repeated-measures ANOVA, analyses of covariance (ANCOVA)) and nonparametric methods (Wilcoxon-Mann-Whitney test, χ^2 ^test of independence and γ measure of association) as needed, based on the data. Holm's modified Bonferroni corrections will be applied to check experimental error (*e.g*., in exploratory analyses). Analyses will be done based on an intention-to-treat basis, whether or not doctors logged and took credits. We will restrict the explanatory analysis to those doctors who took credits. All the analyses will consider *p *= 0.05 as significant (two-sided).

SAS version 9.0 statistical software (SAS Institute, Inc, Cary NC) will be used.

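### The two-by-three ANOVAs have no term for the lot tested and do not say whether the score is combined or lot-specific, so they are not tied to Table 1's lot-specific hypotheses

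*Protocol article*

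**What the plan says.** All places are in the protocol article.

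- **Design.** Under Study design, arm I is trained on lot A and supplies control data for lot B. Arm II is the mirror image: "Group two will have access to ECCE for lot B and will provide control data for lot A".
- **Test content.** Under Outcomes measures and measurements, at each of the three sessions "we will randomly select two vignettes from lot A and two from lot B to avoid repetition". Half of what an ECCE doctor is tested on is therefore untrained material.
- **Hypotheses.** Table 1 states each hypothesis on the scores of one lot. Its classical rows are lot-matched: "Arm I vs. III Complete intervention for lot A (ECCE", and likewise arm II against III on lot B.
- **Block model.** Statistical analyses specifies "one between-subjects factor (ECCE lot A and ECCE lot B) and one within-subject factor (pre-test, post-test one and post-test two".
- **Classical model.** The same section specifies "one between-subjects factor (ECCE set and control) and one within-subject factor (pre-test, post-test one and post-test two) for the classical trial". The abstract describes this comparison as "a classical design (group one and two versus group three".
- **Dependent variable.** It is named only as scores on a single scale ("knowledge test scale will be subjected" to the ANOVA). The section does not say whether the two lots are added together or analysed apart. The planned contrasts it mentions concern retention over time, not lot.

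**The concern.** In a two-by-two incomplete block design, the information about the intervention lies in the crossing of arm with tested content: arm I should gain on A and not on B, arm II on B and not on A. The article lists the ANOVA factors and their levels, and tested lot is not among them. Whether the models test Table 1's hypotheses therefore depends on what the score is, and the text leaves that open.

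Two of the three main hypotheses rest on these models: whether ECCE increases knowledge (block) and whether it is superior to print (classical). An analyst who took the single-scale wording at face value could find no arm difference in the block trial even though ECCE worked, and about half the raw effect against print.

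**Working it through.** **Inputs from the article.** Difference to detect 0.7 SD; two-sided alpha 0.05; power 90%; 45 per arm, raised to 54 for 20% loss; two A and two B vignettes per session.

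**Assumptions not in the article.** Lot scores have SD 1. The correlation r between a doctor's lot A and lot B scores is unknown, so a range is shown. The trained-lot gain is the same at both post-tests and the untrained lot does not change.

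**1. The plan's own figure.** n = 2(1.960 + 1.282)²/0.7² = 42.9, so 43 per arm; the t-based value is 44. The stated 45 is consistent. Power at 45: the SE is √(2/45) = 0.211 and 0.7/0.211 = 3.32, giving 91%. This is an ordinary two-group calculation on one score.

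**2. Block comparison, combined score (mean of A and B).** Arm I gains gA/2 and arm II gains gB/2. The arm-by-time difference is (gA − gB)/2. With gA = gB = 0.7 both arms gain 0.35 and the difference is 0. With unequal gains it measures the difference between lots, which is still not the ECCE effect.

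**3. Block comparison, one lot at a time.** Arm I minus arm II is +0.7 on lot A and −0.7 on lot B. The full effect is recovered, with about 91% power at 45 per arm.

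**4. Classical comparison, combined score.** Arms I and II pooled gain 0.35 and arm III gains 0, so the raw effect is half of 0.7. The SD of the combined score is √((1 + r)/2). The standardised effect is 0.35/√((1 + r)/2), which is 0.495 at r = 0 and 0.35 at r = 1, or 0.71 to 0.50 times the planned 0.7. Power for 90 against 45 falls from 77% (r = 0) to 48% (r = 1).

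**5. Classical comparison, arms I and II pooled on one lot's score.** On lot A, arm I gains 0.7 and arm II gains 0, so the pooled gain is again 0.35. The SE is √(1/90 + 1/45) = 0.183 and 0.35/0.183 = 1.92, giving about 48% power. Lot-specific scoring alone does not rescue this comparison.

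**6. Classical comparison, lot-matched.** The contrast is ½[(A in I − A in III) + (B in II − B in III)], with expectation 0.7 and variance (1 + r/2)/n. At n = 45 and r = 1, the least favourable case, the SE is √(1.5/45) = 0.183 and power is 97%.

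**7. Efficiency of the within-doctor contrast.** Trained minus control lot at a post-test, pooled over arms I and II, has variance (1 − r)/n, against 2/n for a one-lot comparison between arms. The SE ratio is √((1 − r)/2): 0.59 at r = 0.3 and 0.50 at r = 0.5. For change from pre-test, with equal correlation r among all of a doctor's scores, the variances are 2(1 − r)/n and 4(1 − r)/n, so the ratio is √½ = 0.71 whatever r is.

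**8. Simulation.** 4,000 trials, 43 evaluable per arm (54 × 0.8 = 43.2), equal correlation among a doctor's scores, gain 0.7 on the trained lot at both post-tests, 2-df arm-by-time test.

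| Analysis | Rejections, r = 0.3 | r = 0.5 |
|---|---|---|
| Block, combined score | 5% | 5% |
| Block, one lot | 81% | 92% |
| Block, arm x lot x time | 98% | 99.9% |
| Classical, I+II v III, combined score | 62% | 79% |
| Classical, I+II v III, one lot | 31% | 43% |
| Classical, I v III on lot A | 80% | 91% |

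**The case against.** The strongest reply is that the article never says the lots are summed, and much of it suggests they are not. Table 1 words every hypothesis by lot, the use of each arm as control for the other lot requires lot-wise scoring, and the sample size fits a between-arm comparison on one score. With lot-specific scores the stated block ANOVA needs no lot factor and recovers the full 0.7 SD at roughly the planned power. The article also condenses a fuller protocol, where the construction of a score may be set out.

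Most of this stands. A reader might infer that the first main hypothesis goes untested, or that a working programme would inevitably be reported as no difference. The documents do not support that: it follows only if the combined score is used and, for exact cancellation, only if the gains on the two lots are equal. Likewise, halving applies to the raw effect; the standardised loss depends on a correlation the article does not give.

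Two things remain. First, the article does fix the factors and levels, so the missing lot term is part of what it states and not just detail left out. Second, lot-specific scoring does not settle the classical comparison. "one between-subjects factor (ECCE set and control" and the abstract's pooling of groups one and two can be read as a two-level factor, which on either lot's score mixes trained and untrained doctors. The wording does not rule out pooling trained-lot scores, but it does not say so, and it is not reconciled with Table 1.

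**Conclusion.** The concern holds as a conditional one. The models lack a tested-lot term and the score is undefined, so the analysis section does not secure the tests that Table 1 describes.

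- **Combined score:** the block term does not estimate the ECCE effect and rejects at about alpha when gains are equal. The classical raw effect is halved, and its standardised size is multiplied by 0.50 to 0.71.
- **Lot-specific scores:** the block test is valid at full effect size. It yields two answers with no stated way to combine them and forgoes the within-doctor comparison. The classical effect is still halved if arms I and II are pooled on one lot's score.

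The sizes rest on a gain of 0.7 SD confined to the trained lot, unit-variance lot scores and the assumed correlations. Under either reading the text needs changing. Under the more favourable one, the gain for the block comparison is precision and a single pooled answer, not rescue of an invalid test.

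**What to change.** Reword the ANOVA paragraph as follows.

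1. **Score.** State that each session gives every doctor a lot A score and a lot B score.
2. **Block comparison.** Add lot tested (A/B) as a second within-doctor factor, giving arm x lot x time (2 x 2 x 3). Name as the ECCE effect the arm-by-lot contrast at the chosen post-test: change from pre-test, trained lot minus control lot, pooled over arms I and II.
3. **Classical comparison.** Use trained-lot scores only, arm I against III on lot A and arm II against III on lot B, combined in one contrast. Align the abstract's description with Table 1.

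Reporting both contrasts in percentage points with a 95% confidence interval, and adding a vignette term, are optional.

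The cost is one reworded analysis paragraph. Each test already includes vignettes from both lots, so no new data or additional doctors are needed.

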### Study procedures and data collection

The three arms will complete a pre-activity demographic survey, the knowledge tests, and surveys of participation at other educational events. There is growing recognition of EBM in Italy and independent educational initiatives to improve general practice are becoming more common. During the trial, this additional education could be an important threat to internal validity. We will record these concurrent educational experiences in our sample and assess their effects in exploratory post hoc analyses.

Data will be collected from all participants using online instruments. The ECCE platform will manage and track all data collection, following up by e-mail the participants after 16 and 36 weeks. Although researchers are not blinded for the trial group allocation, they will not be able to interfere in collection.

The demographic survey will record sex, age, and years of practice; practice characteristics; preferred CME format; computer skills; ease in using the Internet; familiarity with EB information; frequency of attending residential and distant CME activities.

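### Two variables that arise after allocation, study drop-out and satisfaction, are listed as potential moderators of knowledge scores

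*Protocol article*

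**What the plan says.** The Statistical analyses section plans, as additional work, an "examination of the relationship between knowledge test outcomes and potential moderator variables including sex, age, and years of practice". The list continues with speciality, preferred education format, computer skills and familiarity with evidence-based information. It also includes "study drop-out; satisfaction with learning experience". One set of methods serves the whole list: "we will use parametric methods (regression, repeated-measures ANOVA, analyses of covariance (ANCOVA", followed by nonparametric alternatives, to be chosen as the data require. Nothing separates variables fixed before allocation from those that arise later.

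Other sections show when the two variables arise:

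- **Satisfaction.** Under Outcomes measures and measurements: "All groups will also rate their satisfaction with the information source and its perceived value for their medical education and clinical practice". Under Study procedures and data collection, the content of the pre-activity survey begins: "The demographic survey will record sex, age, and years of practice; practice characteristics; preferred CME format; computer skills; ease in using the Internet". It goes on to familiarity with evidence-based information and attendance at educational activities. Satisfaction is not in it.
- **Drop-out.** The last test is placed at "six months after the intervention (approximately 36 weeks after enrolment, post-test two"). The sample size section expects 20% loss by the end of the study, with 54 doctors randomised per group.

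The main model for the classical comparison has arm as its between-subjects factor and "one within-subject factor (pre-test, post-test one and post-test two) for the classical trial". The block comparison has the same structure. Neither model contains satisfaction or drop-out.

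**The concern.** A moderator analysis asks whether the effect of ECCE differs between kinds of doctor. For the answer to rest on randomisation, the variable that defines the kinds must not itself be changed by allocation.

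Satisfaction fails this test because it is a rating of whatever source the doctor was given. Satisfied users of the printed book and satisfied users of ECCE may be differently selected doctors. Comparing them, or adjusting the arm effect for satisfaction, then gives up the randomised comparison. Drop-out is itself an event of follow-up, and it removes the very score it would be said to moderate.

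What is at stake is a secondary claim in the report, for example that ECCE works better or worse in satisfied doctors, or that its advantage shrinks once satisfaction is taken into account. Such a pattern could come from the conditioning alone. The safeguards in the section do not help. Holm's correction limits false positives but not bias, and the intention-to-treat statement does not protect an analysis that conditions on a later event.

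**Working it through.** **Reference value.** The point rests on no figure stated in the plan. As the true effect I take the plan's own design value, 0.7 SD. It is consistent with the stated sample size: 2 × (1.960 + 1.282)² / 0.7² = 42.9, so 43 per arm by the normal approximation and 44 by the t-test, against 45 stated.

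**Satisfaction.** Assumptions, none of them from the protocol:

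- the arm shifts satisfaction by *a* SD;
- an unmeasured trait, such as motivation, loads *b* on both satisfaction and score;
- satisfaction has no effect of its own on the score;
- both variables have within-arm SD 1.

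Within an arm, the slope of score on satisfaction is then *b*². Holding satisfaction fixed gives

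adjusted arm effect = 0.70 − *a* × *b*².

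| *a* | *b* | *a* × *b*² | Adjusted effect (SD) |
|---|---|---|---|
| 0 | any | 0 | 0.70 |
| any | 0 | 0 | 0.70 |
| 0.3 | 0.3 | 0.027 | 0.67 |
| 0.5 | 0.3 | 0.045 | 0.66 |
| 0.5 | 0.5 | 0.125 | 0.58 |
| 0.8 | 0.5 | 0.200 | 0.50 |

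A simulation of 2,000,000 doctors per setting agreed with the formula to within 0.003 SD, and the unadjusted effect stayed at 0.70. If satisfaction also lay on the causal path to the score, adjustment would remove part of the genuine effect as well.

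**Where *a* is likely to differ from zero.** Arms I and II both rate ECCE, with lots chosen to be comparable, so in the block comparison *a* is plausibly near zero and so is the bias. In the classical comparison, arm III rates print and online text. The protocol itself gives reasons to expect a difference there. The Study design section warns that allocation to control can demotivate, Table 1 concedes that the classical comparisons do not control the Hawthorne effect, and the Discussion names boredom as a barrier to reading *Clinical Evidence*.

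**Drop-out.** The scores available depend on when a doctor is lost:

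| Lost | Pre-test | Post-test one (about 16 weeks) | Post-test two (about 36 weeks) |
|---|---|---|---|
| before post-test one | yes | no | no |
| between the post-tests | yes | yes | no |

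The drop-out group has an empty cell at post-test two, so an arm-by-drop-out effect on that score cannot be estimated. At the planned loss this concerns 0.20 × 54 = 10.8, about 11 doctors per arm, or 0.20 × 162 = 32.4, about 32 in all. These doctors lack a final score whether or not drop-out is on the list. The number shows only whom the planned analysis could not reach.

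**The case against.** The best defence is that the word moderator is used loosely. The text commits only to examining a relationship, and its methods include plain measures of association chosen as needed. It nowhere says that the arm effect will be adjusted for satisfaction or reported within levels of it. This stands. A reader might infer that the plan will produce a biased effect estimate, but the document shows only that it allows one, in additional analyses. A reader might also infer that the primary result is at risk. It is not, since the main ANOVA contains neither variable.

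On drop-out, the planned outcomes are the knowledge tests in the plural, and doctors who leave have earlier scores. Relating drop-out to those scores is ordinary attrition analysis. This also stands. The tempting conclusion that a drop-out analysis can say nothing about the doctors who left goes too far, because only the scores missing after loss are out of reach.

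The size of any bias is likewise an illustration. The protocol gives neither *a* nor *b*, and it states no SD of the test score, so the result cannot be turned into score points. How missing scores enter the main analysis is a separate matter, which may be settled in documents not shown.

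The defence does not remove the wording. The section calls both variables potential moderators, puts them in one list with baseline traits, and names regression and ANCOVA for that list. An analyst who follows it literally would condition on a consequence of allocation. Even a plain association with satisfaction would need a separate label.

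**Conclusion.** The point holds for the additional analyses only. Satisfaction and drop-out arise after allocation and do not belong in a list of moderators. Conditioning on satisfaction can bias the ECCE effect, chiefly against arm III. For the bias to arise, the arm must affect satisfaction, and satisfaction must either share causes with the score or lie on the path to it. In the illustrated settings with both *a* and *b* above zero, the loss is 0.03 to 0.20 SD out of 0.70. Its direction and size depend entirely on the assumed values. Drop-out cannot moderate the post-test two score, though it can be described through earlier scores. No sample size, significance level or primary estimate changes. This is a free improvement.

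**What to change.** In the Statistical analyses section:

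1. Restrict the moderator list to variables that pre-date allocation, and remove study drop-out and satisfaction from it.
2. Report satisfaction as an outcome by arm.
3. In place of drop-out as a moderator, give a descriptive comparison by arm of drop-out rates and of the available earlier scores of those who dropped out (pre-test, and post-test one where taken).

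The cost is a change of wording and one small table. No new data are needed, because the platform already collects the ratings, the test scores and the follow-up status.
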